**Table 1. Sequence Timeline for the Eight Planned Experimental Gardening and Art Sessions.**

**Session Timeline**

| Timeline | Session Component |
| --- | --- |
| 0 min | Arrival and Sign-in/Pick up Name Tag |
| 0-10 min | Individuals Review Previous Activities (i.e. plant growth or art projects)/Instructors Greet Individuals and Assemble Group/Heart Rate and Blood Pressure Measurements Recorded |
| 10-20 min | Educational Module/Introduction to Activity/Demonstration of Activity as Warranted (booklet, instruction sheet, resource material handouts) |
| 20-50 min | Gardening or Art Activity, Questions |
| 50-70 min | Clean-up/Heart Rate and Blood Pressure Measurement Recorded/POMS and PSS Assessments (Even-numbered sessions) and BDI (Sessions 4 and 8)/Departure |
| 70-95 min | Session Review and Record Notes and Observations (Staff only) |

The GA sessions will be conducted inside the Wilmot Gardens 2700 sq. ft. greenhouse to increase control of and uniformity of environmental conditions compared to conducting sessions outside. Ambient environmental conditions for temperature and humidity in the greenhouse will be recorded at the beginning and end of each gardening session to provide information about the conditions over the duration of the gardening treatments. An evaporative cooling system and automated, adjustable shade cloth will be used to keep the greenhouse in a comfortable range for participants, and water fountains are located nearby for participants to keep hydrated throughout the sessions. Outside weather conditions during the scheduled gardening sessions will also be noted as sunny, overcast, rainy, hot or cold, low or high humidity. A restroom is readily accessible in the adjacent lobby of the greenhouse at the front of the structure. Art sessions will be conducted in the air-conditioned Wilmot Gardens Conference Center 1032 sq. ft. conference room that has the capacity to comfortably fit approximately 35 seated people or 10 art session participants and art materials and stands. The conference center is equipped with a kitchenette and accessible bathrooms.

Following the conclusion of each gardening and art session, the leader/study staff of the session will record de-identified notes of informal observations made during the session (see Post-Session Review Form Gardening and Art Study). The review will consider general group interest, engagement and participation in the activities, and note unsolicited feedback from unidentified participants such as “I had fun” or “I liked planting seeds” or “I liked last week’s activity better than today’s,” or whether participants are interactive with other participants in the group activities.

**Gardening Activities (GAs):** Participants assigned to the gardening treatment group will receive eight individual gardening activity sessions (see Gardening Activity Session 1 example in Table 2) over a period of 4 weeks equating to two sessions per week. Additionally, there will be an orientation session before and a wrap-up session after the eight gardening sessions. The individual sessions will take place at the same time of day on Mondays and Wednesdays or on Tuesdays and Thursdays. The individual sessions are designed to fit together within the larger context of the overall experimental treatment. The experimental treatment is configured to introduce and reinforce a limited number of different gardening themes that include: 1) propagation that will be presented in two forms (seeds/bulbs/tubers and cuttings/division); 2) transplanting; and 3) simulated harvest and sensory stimulation. The sensory stimulation theme will be coupled to an educational component about the plants providing the sensory stimulation. The emphasis and reinforcement of the selected gardening themes will be achieved using different types of plants with different uses and characteristics in the different sessions. The participants will be given a free copy of the “Florida Gardener’s Handbook” by MacCubbin, Tasker, Bowden and Lampl’l (2012) (see file of front cover of the book and Table of Contents, Florida Gardeners’s Handbook Cover ToC) that will provide some general background information on the plants used in the GAs. The purpose for supplying the handbook is to provide a more complete gardening and educational experience to complement the hands-on activities in the greenhouse. The activities for all of the individual sessions are designed to involve approximately the same level of physical, cognitive and social engagement to filter out differential competing interacting effects in these aspect areas. Participants will receive a handout booklet (see Gardening Sessions Booklet) for each of the eight sessions that will provide instructions and information for each of the GAs being experienced (see Session 1 Gardening Activity Handout and Instructions Exemplar). Table 2 below provides a detailed example of Session 1 and is generally representative of the information, as well as the educational, social and physical purposes, goals and benefits associated with the eight gardening sessions. A more complete description for all gardening sessions can be found in the supporting documents (see Eight GA and AA Sessions Descriptions) which may undergo some minor changes and adjustments based on availability of plants and/or other gardening materials or as needed to optimize the effectiveness of a given session activity.

**Table 2. Gardening Activity Session 1 Exemplar: Educational Purpose, Anticipated Social Interactions, Specific Goals and Benefits to the Participants.**

**Session and Activities**

| Session 1 | PROPAGATION: Planting Seeds of Herbs and Scented Plants (e.g. basil, borage, chives, dill, oregano, rosemary and thyme)(seedlings can be used for session 7) |
| --- | --- |

**Educational Purpose:** This exercise will highlight a group of plants widely used in culinary practices and prized for their sensory stimulating attributes. Instruction will explain the role and significance of seeds in plant reproduction, propagation, and the development of a plant from a seed, and show variation in plant seed morphology, size, shape and tactile characteristics, demonstrate sowing methods, and observe the rate of germination of different species. Participants will learn how to sow seeds and what materials are needed to begin growing herbs and scented plants for use at home.

**Social Interactions:** Participants will interact with session leaders and co-participants. Mechanism for interactions will include questions and comments between leaders and participants. Participants can be asked to share with the group their favorite herbs and scented plants, including any recipes for herbs. Participants will need to pass seeds to other participants who would like to plant those various varieties. Participants may be asked to work in pairs or small groups in order to share limited materials and tools. In this first session, participants will also be asked to share their first name only with the group.

**Goals/Benefits:** Facilitate participant-plant interactions, increase knowledge about plants and planting seeds; stimulate cognitive abilities and skills; increase concentration, restore directed attention; experience visual, tactile and olfactory sensory stimulation, enhance motor skills (hand-eye coordination and fine motor function); experience group interactions; and enjoy the activity.

____________________________________________________________________________

**Art Activities (AAs):** Participants randomly assigned to the art comparison group will receive eight individual art activity sessions (see Art Activity Session 1 example in Table 3) over a period of four weeks with two sessions per week. Additionally, there will be an orientation session before and a wrap-up session after the eight art sessions. The individual art sessions will take place at the same time of day on Mondays and Wednesdays or on Tuesdays and Thursdays as the gardening sessions. The participants will be given a free copy of the “The Artist’s Handbook” by Ray Smith, 3^rd^ Edition, (2009) (see file of front cover of the book and Table of Contents, The Artist’s Handbook Cover ToC) that will provide some general background information on the art media and tools used in the AAs. The purpose for supplying the handbook is to provide a more complete art and educational experience to complement the hands-on activities taking place in the conference center. The activities for all the individual art sessions are designed to involve approximately the same level of physical, cognitive and social engagement as the gardening intervention in an effort to filter out differential competing interacting effects in these aspect areas. Participants will receive a handout booklet (see Art Sessions Booklet) for each of the eight sessions that will provide instructions and information for each of the AA being experienced (see Session 1 Art Activity Handout and Instructions Exemplar). Table 3 below provides a detailed example of Session 1, and is representative of the information, as well as the educational, social and physical purposes, goals and benefits associated with the eight art sessions. A description for all art sessions can be found in the supporting documents (see Eight GA and AA Session Descriptions) which may undergo some modification or changes and adjustments based on availability of supplies and/or other art materials or as needed to optimize the effectiveness of a given session activity.

**Table 3. Art Activity Session 1 Exemplar: Educational Purpose, Anticipated Social Interactions, Specific Goals and Benefits to the Participants.**

**Session and Activities**

| Session 1 | PAPERMAKING: Making Paper from Recycled Materials |
| --- | --- |

**Educational Purpose:** This exercise will explore basic handmade papermaking techniques and highlight one of the oldest recycling practices. Paper dates back to 105 AD in China and was made by hand until industrial manufacturing in 1803. Hand papermaking continues to be a specialized craft today, and is widely used as a medium for artistic expression. Participants will learn how to create a paper pulp from recycled papers and cotton linter using a household blender. They will experiment with color options and provided additives before pulling sheets of handmade paper using a dip hand mold. Papers will be transferred to couch sheets and left to dry until a subsequent workshop. Participants will also be shown a basic pour method utilizing a tin can mold to increase accessibility of papermaking at home without specialized materials.

**Social Interactions:** Participants will interact with session leaders and other participants. Mechanism for interactions will include questions and comments between leaders and participants. Participants will be sharing pulp vats and additives with one another. In this first session, participants will be asked to share their first name only with the group.

**Goals/Benefits:** Facilitate participant-art medium interactions, increase knowledge; stimulate cognitive abilities and skills; increase concentration; experience visual and tactile sensory stimulation, enhance motor skills (hand-eye coordination); experience group interactions; and enjoy the activity.

____________________________________________________________________________

**The Health and QOL Evaluations:** Gardening programs and horticultural therapy have been linked with reduced levels of anxiety, depression, pain, and stress, and lower heart rate, and improved cognitive function, self-esteem, physical and mental health and quality of life. Similarly, art programs and art therapy have been linked to improvements in positive and negative affect, anxiety, self-esteem, depression symptomatology, and quality of life (Uttley et al 2015). The impacts of the treatment regime on participants will be evaluated with several self-report assessment instruments that have been properly licensed or purchased. The standard SF-36 Health Survey instrument (Ware and Sherbourne 1992; Hays et al 1993) will be used to evaluate eight scales that link to physical and mental health over a four-week recall interval. To gain information relative to stress, the study will use the Perceived Stress Scale (PSS) (Cohen et al 1983) with a recall interval of one week. To gain insight relative to the intensity of depression, the study will use the Beck Depression Inventory 2^nd^ edition (BDI-II) (Beck et al 1988) with a recall interval of two-weeks. To gain information relative to anxiety, the study will use the State Trait Anxiety Inventory (STAI) instrument (Form Y) (Spielberger et al 1983). The STAI reports on *“at this moment”* status. The study will also use the POMS 2-A® short form instrument (McNair et al 1981; Shacham 1983) to assess the mood states of individuals in an effort to examine changes in mood during the course of the treatment. The POMS reports on *“at this moment”* status with regard to mood disturbance. The Profile of Mood States™ provides self-report scales that allow for the assessment of transient, fluctuating feelings, and enduring affect states. The tool is applicable in settings where sensitivity to change is needed to assess treatment progress monitoring and evaluation. The Satisfaction with Participation in Discretionary Social Activities (SPDSA) PROMIS short form v1.0 instrument will be used to assess contentment with participants’ leisure time and affairs with friends, and encompasses a recall interval of one week. The SF-36, PSS, BDI-II, STAI, POMS 2-A Short, and SPDSA instruments will be administered prior to the beginning and following the completion of the gardening and art sessions treatment regime during visits 2 and 11. In addition, for both the GA and AA groups the POM 2-A Short and PSS instruments will be administered on a weekly basis at the conclusion of the 2^nd^, 4^th^, 6^th^ and 8^th^ gardening and art sessions during visits 4, 6, 8 and 10 to provide a time-course of mood and stress status, respectively, during the experiment. The BDI-II will be administered at the conclusion of the 4^th^ and 8^th^ gardening and art sessions during visits 6 and 10 to provide information on the depression status during the experimental regime. Heart rate and blood pressure measurements will be made at the beginning and end of visits 2-11.

**Data Collection:** The study team will collect baseline data on each subject prior to the beginning of the gardening or art activity sessions by administering various assessments during the orientation session, visit 2. In a final wrap-up session, visit 11, we will repeat the data collection, administering the complete battery of assessments following participation in the 8^th^ and final activity session of the program. Assessments of the participants will be in the form of self-administered health-related questionnaires, a discretionary social activities questionnaire, and heart rate and blood pressure monitoring. Trained research study staff will administer questionnaires. Heart rate monitoring for each participant will be accomplished for each session by way of BP wrist cuff readings and heart rate monitoring with the Omron 7 monitor (BP and HR) wearable. Two to three measurements will be taken at the beginning and at the end of each session.

**Other Study Procedures:** If a study participant completes a health and psychometric assessment instrument, and the study staff sees that their responses indicate depressive or anxiety symptomatology, the study staff will recommend that the individual seek professional help.

**Incidental Findings:** No incidental findings are anticipated, but if an incidental finding is made, the participant will be given a direct referral for medical follow-up. The results from the medical follow-up and review will not be provided by the service to the PI.

Anytime a health and psychometric assessment instrument is completed and the study staff sees responses that indicate depressive or anxiety symptomatology, the study staff will recommend the participant seek professional help. In the event that evaluation of the BDI-II or STAI responses suggests a risk of self-harm or suicidal behavior by a study participant, a qualified mental health professional arranged by the study staff irrespective of day and time will immediately evaluate the individual. Study staff will assist as needed to access emergency care at a recognized mental health treatment facility.

**Community Outreach Recruitment Campaign:**

The study recruitment campaign will encompass, as necessary, all of the following recruiting steps that will invite women to contact study staff if interested in participating in the study:

- Distribute and post flyers in the Gainesville community (see Gardening and Art Study Flyer) (e.g. churches, gyms, coffee shops, local bulletin boards, Haile plantation and downtown Gainesville farmers markets, bus stations, college campuses, UF Health complexes including UF Health Springhill, parks e.g. Depot Park). See flyer locations map for more community flyer areas: <https://www.google.com/maps/d/edit?mid=1JS_DWETw3aG-A4Dv2fbO1Wqg95k&ll=29.661801102895165%2C-82.39106939999999&z=11> .
- If necessary, contact local radio stations to read public service announcement script (e.g. WUFT) (see Gardening and Art Study Radio PSA Script).
- If necessary, contact local newspapers to run print advertisement (e.g. Gainesville Sun) (see Gardening and Art Study Print Ad Script).
- Post approved flyer (see Gardening and Art Study Digital Flyer) to newsletters or bulletin boards:
  - Contact the Center for Gender, Sexualities, and Women’s Studies Research to place a study recruitment flyer in their newsletter or send out flyer to mailing list.
  - Contact the University Women's Club organization comprised of faculty and staff and wives of faculty and staff of the University of Florida, and of women who actively support the mission and goals of the Club. Inquire if study could send an announcement for inclusion in their September newsletter. <http://universitywomensclub.ufl.edu/>
  - Contact Alachua County Extension, Master Gardener Coordinators, colleagues in plant sciences, and botanical gardens and send informational flyer about study, asking them if they would distribute flyers or post in their bulletin boards or newsletters.
  - Contact American Association of University Women to provide flyer and information about study, ask to include in newsletter or share with mailing list.
- Provide flyers to UF Health Women's Center – Springhill <https://ufhealth.org/uf-health-womens-center-springhillhill>.
  - And Women and Wellness Classes (North Florida Regional Medical Center).
- Contact UFHealth Integrative Medicine send flyers to <https://ufhealth.org/integrative-medicine/about-us> to make available to wellness classes and distribute around facilities.
- Submit UF StudyConnect request form to Clinical and Translational Science Institute <https://www.ctsi.ufl.edu/research/participant-recruitment/uf-studyconnect/> to display study on UFHealth.org Research Studies and Clinical Trials and UF StudyConnect pages.
- Communicate with HealthStreet: <http://healthstreet.program.ufl.edu/> to coordinate community recruitment.
- Post study details on ResearchMatch.org.
- If recruitment is insufficient following distribution of flyer and radio announcement, we will use a targeted GoogleAd service to target advertisement based on key word searches such as gardening, health and fitness, salad recipes and others to zip codes in Gainesville, FL (see Gardening and Art Study GoogleAd). The GoogleAd Campaign will show the Study ad based on the study flyer, and anyone interested in the study will click on the link (URL) in the ad. The link will be to a webpage on the Environmental Horticulture Department server where it will display the approved Gardening and Art Study Digital Flyer.
- To assist in sharing information about the study, a Gardening and Art Study Information Sheet has been prepared to share with potential volunteers that have requested additional information beyond that contained in the Gardening/Art Study Flyer, but before the Study Staff has contacted an interested party for the scripted phone interview. The information sheet was prepared using content from the approved phone interview script.

**Informed Consent and Screening:**

When interested community members contact study staff by phone, study staff will follow an approved script when returning phone calls (see Gardening and Art Study Phone Script). The phone conversation will include a description of the study, inquiry of the community member’s interest in participation, and assessment of eligibility requirements. Individuals that meet basic eligibility criteria will be invited to schedule an in-person meeting at a private location (a private office or room in Fifield or Mehrhof Hall on the UF campus will be suggested, but other locations will be considered as necessary).

Individuals that decide to attend the in-person meeting will be consented and given an eligibility/screening questionnaire (see In-Person Eligibility Screening Questionnaire Gardening and Art Study) and demographic questionnaire (see Participant Demographic Questionnaire). Study staff will inform the study volunteer that an email and/or phone call will be sent to relay information on volunteer’s status in the study. Volunteers will be given a phone number to contact study staff if they are interested in their status in the study and if they want to follow-up with any questions for the study staff (e.g. asking about which group they have been randomly assigned).

If study volunteers are eligible, they will be randomly assigned to either the gardening or art group and invited to attend an orientation session (visit 2) that includes a tour of the facilities, parking instruction, rules of the experiment, introductions of the group members to study staff and other members of the groups. This is also when baseline psychometric assessments and heart rate and blood pressure measurements will be given.

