The experimental design of the study is upgraded from the previous gardening study protocol executed in spring 2015. Previously, the design implemented a protocol in which women self-selected to be in a treatment group or non-active control group. The current design includes the alternate, comparable group of art activity. Eligible volunteers will be screened, consented, selected and enrolled in the study. Participants will then be randomly assigned to receive either the gardening treatment intervention or art intervention. Further participant assignment into two subgroups of gardening and art will be random, but it may be necessary to adjust some assignments to accommodate participant schedules. Both treatment groups will undergo the same self-report psychological and social assessments and physiological measures along the same timeline with congruent intervals of administration.

If study volunteers are eligible, they will be enrolled in the study and invited to attend an orientation session for either the art or gardening groups that includes a tour of the facilities, parking instruction, rules of the experiment, introductions of the group members to study staff and other members of the groups. This is when baseline psychometric assessments will be given.

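### The only baseline measurement comes after randomisation, at an arm-specific orientation where participants can already know their arm

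*Protocol*

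**What the plan says.** Two sections of the Protocol give the same sequence.

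- **Staging of Experimental Gardening and Art Programs** (under Research Plan): volunteers are screened, consented, selected and enrolled. "Participants will then be randomly assigned to receive either the gardening treatment intervention or art intervention". They are then "invited to attend an orientation session for either the art or gardening groups that includes a tour of the facilities". Of that session it says: "This is when baseline psychometric assessments will be given".
- **Informed Consent and Screening**: once eligible, "they will be randomly assigned to either the gardening or art group and invited to attend an orientation session (visit 2"). The session includes "introductions of the group members to study staff and other members of the groups". It continues: "This is also when baseline psychometric assessments and heart rate and blood pressure measurements will be given". Volunteers also receive a telephone number for questions, and the example given is "asking about which group they have been randomly assigned".

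Data Collection also places baseline at the orientation, visit 2. The preceding in-person meeting collects only an eligibility questionnaire and a demographic questionnaire. The Health and QOL Evaluations section schedules heart rate and blood pressure at the start and finish of every visit from 2 to 11. It describes the POMS and STAI as momentary. The recall periods of the others are one week (PSS, SPDSA), two weeks (BDI-II) and four weeks (SF-36).

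**The concern.** What the Protocol calls baseline precedes the first activity session but follows randomisation. Allocation is open, can be asked for by telephone, and is evident at the latest when a participant arrives at an orientation for one arm. Pleasure or disappointment about the arm can therefore enter the baseline score. Such a reaction need not be equal in the two arms. Part of the recruitment runs through Master Gardener coordinators, botanical gardens and plant-science colleagues, with gardening-keyword advertising in reserve, although those enrolled must be neither gardeners nor artists.

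The hypotheses under Specific Aims are framed as alteration, improvement or reduction, so they look to change from a starting value, and visit 2 is the only pre-programme measurement. An arm-related shift there passes into any change-from-baseline contrast and, in part, into any baseline-adjusted contrast. Adjustment cannot remove it, because the covariate is itself measured after randomisation. Nothing done after data collection can recover a pre-allocation value.

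**Working it through.** **Sequence.** Both sections that describe enrolment give the order enrol, randomise, invite to the arm's orientation, measure baseline. Data Collection is consistent with this. No section describes an outcome measurement before allocation, and none withholds the arm until the battery is done. That participants know their arm at visit 2 is an inference from the open allocation, the telephone enquiry and the arm-specific session. The Protocol does not say it in one sentence, but the inference is strong.

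**Order within visit 2.** The Protocol does not say whether the questionnaires come before or after the tour and introductions. Heart rate and blood pressure have an opening reading, which may precede the tour but still follows allocation.

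**Size, as an illustration only.** The Protocol has no figure on this point. Its minimum of 12 to 17 participants cannot be reproduced, because effect size, SD, alpha and power are not given; the point does not depend on it.

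- From the Protocol: n = 20 per arm (Study Sample Size).
- Assumed: two-sided alpha 0.05; no true effect; unit SD at both times; baseline-outcome correlation r = 0.5 or 0.7; a baseline shift of s SD in one arm only, gone by visit 11; normal approximation.

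Change scores: bias = s; SE = √[2(1 − r) × 2/n]. For r = 0.5, √(2 × 0.5 × 0.1) = 0.316. For r = 0.7, √(2 × 0.3 × 0.1) = 0.245.

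ANCOVA: bias = r × s; SE = √[(1 − r²) × 2/n]. For r = 0.5, √(0.75 × 0.1) = 0.274. For r = 0.7, √(0.51 × 0.1) = 0.226.

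Rejection rate = 1 − Φ(1.96 − bias/SE) + Φ(−1.96 − bias/SE).

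Example, change score, s = 0.3, r = 0.7: bias/SE = 0.3/0.245 = 1.225, so the rate is 1 − Φ(0.735) + Φ(−3.185) = 0.231 + 0.001 = 0.232.

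| Shift s (SD) | Change-score bias | Change-score rejection, r = 0.5 / 0.7 | ANCOVA bias, r = 0.5 / 0.7 | ANCOVA rejection, r = 0.5 / 0.7 |
|---|---|---|---|---|
| 0.1 | 0.10 | 6.2% / 6.9% | 0.05 / 0.07 | 5.4% / 6.1% |
| 0.2 | 0.20 | 9.7% / 12.9% | 0.10 / 0.14 | 6.5% / 9.5% |
| 0.3 | 0.30 | 15.8% / 23.2% | 0.15 / 0.21 | 8.5% / 15.3% |

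A simulation of 20,000 trials under the same assumptions agrees closely. Change-score rejection was 9.6% and 12.7% at s = 0.2, and 15.0% and 22.6% at s = 0.3. ANCOVA bias at s = 0.3 was 0.149 and 0.213.

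For scale, 20 per arm has 80% power for a difference of (1.960 + 0.842) × √(2/20) = 0.886 SD.

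If baseline is measured before allocation is made or disclosed, the expected between-arm difference at baseline is zero, and so is the bias in both analyses.

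**The case against.** The case against a strong reading has several good points.

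- **Both arms are active.** They share the same visit-2 structure and payment. A reaction common to both arms cancels. A preference effect that lasts unchanged to visit 11 also cancels from change scores, leaving an ordinary open-label effect that re-ordering cannot cure. This stands: the illustration needs a one-sided shift that fades.
- **Most questionnaires are not momentary.** Four of the six have one- to four-week recall, including the SPDSA on which the second hypothesis rests. This stands and narrows the exposure.
- **No analysis model is fixed here.** The bias is smaller under ANCOVA, and under the same assumptions a comparison of post-treatment scores alone would not carry it. This also stands.

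A reader might infer that the tour and introductions have contaminated the baseline. The documents do not support that, because the questionnaires are nowhere placed after the tour and an opening heart rate and blood pressure reading exists.

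A reader might also infer that women who dislike their arm disappear uncounted before visit 2. That is not shown either. Enrolment precedes randomisation, a study ID is assigned after consent, demographic data are collected at the in-person meeting, and destruction of forms or data applies only to ineligible people. Study Sample Size speaks of consented volunteers who fail eligibility or do not continue; it does not classify randomised women who decline visit 2. Such a woman would, however, have no outcome data.

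None of these points supplies a baseline taken before allocation.

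**Conclusion.** The point holds as a weakness of the stated sequence: the sole baseline is post-allocation and can be affected by knowledge of the arm, chiefly for the POMS, STAI, heart rate and blood pressure. It shows possible bias, not expected bias. No shift is estimated in the documents, and its size and direction are unknown. Under the stated assumptions, the effect on type I error runs from almost nothing (about 5-7% at 0.1 SD across the two analyses) to material (16-23% for change scores and 8.5-15% for ANCOVA at 0.3 SD). Reading 0.3 SD as the likely value would go beyond the documents. The change is worth making before enrolment because the defect cannot be repaired afterwards and the remedy is cheap.

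**What to change.** Amend Staging of Experimental Gardening and Art Programs, Data Collection, and Informed Consent and Screening so that the full battery, heart rate and blood pressure are completed after consent and confirmed eligibility but before allocation is made or disclosed. Either of two routes would do:

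1. Measure at the existing in-person screening meeting, before randomisation. The visit numbering in The Health and QOL Evaluations would then need to follow.
2. Measure at the very start of visit 2, with the arm withheld from telephone replies, emails and the invitation until the battery is complete. The arm-specific introductions and tour come afterwards.

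A joint visit 2 for both arms of a day slot is one way to do the second. At most 10 + 10 = 20 people would attend, and the conference room seats about 35. It is an option, not a requirement, and the Protocol gives no visit-2 staffing or duration from which to cost it.

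State also that anyone randomised who does not attend visit 2 will be reported by arm.

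Cost: small edits to the telephone script and invitation, and either slightly later disclosure of the arm or a longer screening meeting.
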